## Participant and Data Confidentiality

Every effort will be made to ensure participant confidentiality. Leadership at participating clinics will not be informed about any information regarding participation in the study. All of the personnel and staff on the study team have been certified in NYU’s Human Research Social/Behavioral Research Course through the CITI program. The study team recognizes that the protection of human subjects relies on policies that secure data with personally identifiable information. Each of the investigators has adopted, and will strictly follow, such policies for all data used in the study. Any time data is reported, it will be aggregated with that of other respondents (e.g., to discuss identified themes or key concepts) and never reported with personally identifiable information. No information will be reported that could make it possible for anyone to identify participants in any presentations or written reports about this study. Any identifiable personal information that participants may reveal about themselves during the interviews will be removed from the transcripts. If a direct quote from an interview is utilized in a report or publication (e.g., to exemplify a concept that arose in multiple interviews), it will only be cited using a pseudonym or participant ID number. All information will be stored in our secure, encrypted NYU drives. Personal identifying information will never be shared with anyone outside of the research team.

Information about study subjects will be kept confidential and managed according to the requirements of the Health Insurance Portability and Accountability Act of 1996 (HIPAA). Those regulations require a signed subject authorization informing the subject of the following:

- What protected health information (PHI) will be collected from subjects in this study
- Who will have access to that information and why?
- Who will use or disclose that information?
- The rights of a research subject to revoke their authorization for use of their PHI.

In the event that a subject revokes authorization to collect or use PHI, the investigator, by regulation, retains the ability to use all information collected prior to the revocation of subject authorization. For subjects that have revoked authorization to collect or use PHI, attempts should be made to obtain permission to collect at least vital status (i.e. that the subject is alive) at the end of their scheduled study period.

# Data Handling and Record Keeping

## Data Collection, Confidentiality and Management Responsibilities

Following each interview, digital audio files of the interviews will be transcribed by Research Assistants at NYU Langone. After transcripts are checked for accuracy, audio files will be destroyed and only transcripts will be stored on a secure MCIT managed network shared drive. Contact information will be stored on a MCIT-managed network drive.

We recognize the importance of providing a plan to ensure scientific integrity and safeguard the well-being of study participants. Because the current study poses little risk to the participants, does not involve blinding of providers or participants, and does not involve a drug trial, we believe that the study qualifies for monitoring at the level of the PI. During the informed consent process, participating interviewees and their office staff will be informed that any breach of confidentiality needs to be reported to the Project Director. If any participant appears to be at risk in any way as a result of participation in the study, the IRB at NYU Langone will be notified as soon as the immediate needs of the individual have been addressed.

Subject confidentiality is held in strict trust by the research team. It is the responsibility of the Principal Investigator to oversee the study at his site.

Every effort will be made to ensure participant confidentiality as prescribed by the NYU Grossman School of Medicine Institutional Review Board and HIPAA standards. All of the personnel and staff on the study team have been certified in human subjects education from the CITI program. The study team recognizes that the protection of human subjects relies on policies that secure the data with personally identifiable information and that limit the release of analysis and results to aggregations and estimated parameters that cannot reveal information about an individual. Each of the investigators has adopted, and will strictly follow, such policies for all data used in the study.

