We plan to obtain verbal consent prior to conducting the interview. The team has decided to obtain verbal consent as consent will be obtained immediately before interview begins. The key information sheet and verbal consent script will be provided to participants prior to the interview and the verbal consent will be read to participants verbally. Verbal consent reduces unnecessary burden on the participants; therefore, we have chosen to obtain verbal consent over e-consents. Participants are always given permission to not answer questions with which they feel uncomfortable. Data collected at the staff level will be non-invasive and similar to what they would experience in the course of their treatment provision or daily work. Participation will not affect daily work and supervisor or clinic staff at respective clinics will not be informed about who is participating in this study. We will not share any information from the interviews with the clinic or staff unless in aggregate, de-identified form. The probability and magnitude of harm or discomfort for the interviewees anticipated in the study are not greater in and of themselves than those ordinarily encountered in daily life. Records of participation in this study will not be connected to residential facility staffs’ employment record. Confidentiality of the participants will be protected in several ways. All participants will receive an identifying number for coding and analyzing data. Identifying code numbers will be kept in a separate file from completed transcripts. Data will be reported in clinic-level format only. Any other potentially identifying information will also be removed (e.g., specific information about unusual characteristics or events that may be known in the community). All data will be kept in a locked file and will be accessible only to the research team. Participants’ names and identifying characteristics will not be used outside of the NYU site.

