## Vulnerable Subjects

No vulnerable subjects will participate in the qualitative interviews. We will not be interviewing staff of NYU Langone Health; thus, participants are not classified as a vulnerable population. Still, interviewees may feel obliged to complete the questionnaire and the interview if recommended by their organization. We will not be reporting back to leadership on participants therefore they will remain unaware of who agreed to participate and who did not.

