## Consent Procedures and Documentation

Prior to scheduling interviews, we will send key information sheets and verbal consent script to any potential participants. Potential participants can, then, agree to schedule a time to speak and each staff member will be asked to provide verbal consent if they are still willing to participate in the interview. At the beginning of each interview, the interviewer will use the verbal consent script to: explain the purpose, risks, and benefits of the study, address any questions or concerns the participant may have, and obtain the participant’s verbal informed consent to participate in the interview and be audio-recorded. We prefer a verbal consent process as this poses less burden to the participants. It will also allow participants to ask questions before they agree to participate in the study. Because we will be using a verbal consent process, we are requesting a documentation of consent waiver (attached).

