Project data will be made available to the Data Ecosystem in a manner that is consistent with Data Use Agreements with the data owners. The data owners are only permitted to share these data at the person level as long as it supports the administration of the Medicaid program. Generally, we will be able to submit reports that present statistical data at an aggregate level in a form permissible and approved by the owner. The data for the quantitative components of this study will be culled from the administrative data files of the New York State Office of Alcoholism and Substance Abuse Services (OASAS) and the New York State Department of Health (DOH). Due to the nature of the data security agreements between OASAS/DOH and NYU HEAL, we will not be able to make person-level data available for sharing. Subject to approval from the Department of Health and OASAS, we can provide tables of data summaries categorized by demographic, geographic, and provider characteristics.

We will be able to provide summary reports from qualitative data since the number of participants is small and the risk of being identification is high. The proposed qualitative research will include data from approximately 174 addiction treatment staff and 144 patients being interviewed about take-home dosing practice changes after the intervention has been implemented. The final dataset will include self-reported demographic and experience data. Even though the final dataset will be stripped of identifiers prior to release for sharing, there remains the possibility of deductive disclosure of participants with easily identifiable characteristics which could possibly affect participants’ employability. This is especially the case because the data will be collected from a small number of staff at each participating clinic and it may be known by the provider community which clinics in each identified region are participating in the study.

Thus, we will make the data and associated documentation available to users who request it in writing only under a data-sharing agreement approved by study co-investigators that provides for: (1) a commitment to using the data only for research purposes and not to identify any individual participant; (2) a commitment to securing the data using appropriate computer technology; and (3) a commitment to destroying or returning the data after analyses are completed. This data sharing plan will be made clear in consent documents for participants.

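### Section 10.1 brings interviewees' office staff into the consent process, which can reveal which staff are interviewed; the rules on sharing interview data also need to be reconciled

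*Protocol*

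**What the plan says.** **Office staff and consent.** Describing what happens when consent is taken, Section 10.1 states that "participating interviewees and their office staff will be informed that any breach of confidentiality needs to be reported to the Project Director".

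Three other sections bear on who may learn of a person's participation:
- Section 2.3.1 (Known Potential Risks): "supervisor or clinic staff at respective clinics will not be informed about who is participating in this study".
- Section 5.3 (Vulnerable Subjects), speaking of leadership: "they will remain unaware of who agreed to participate and who did not".
- Section 9.5 (Participant and Data Confidentiality): "Leadership at participating clinics will not be informed about any information regarding participation in the study".

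Section 9.4 (Consent Procedures and Documentation) sets out how consent is taken. Materials are sent beforehand, a time is agreed, and "each staff member will be asked to provide verbal consent if they are still willing to participate in the interview". The interviewer reads the script at the start of the interview. Nobody else at the clinic has a part in it.

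**Sharing of interview data.** Section 10.4 (Publication and Data Sharing Policy) says the team can "provide summary reports from qualitative data since the number of participants is small and the risk of being identification is high". It then describes a final dataset of participants' own demographic and experience data with identifiers removed, concedes that some people could still be identified by deduction, and concludes that "we will make the data and associated documentation available to users who request it in writing only under a data-sharing agreement". The agreement must bar re-identification, require secure handling, and require the data to be destroyed or returned. The plan is to be explained in the consent documents.

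**The concern.** The Section 10.1 sentence concerns people who are already participating interviewees and places the contact with their office staff inside the consent process. Consent is taken person by person at the interview. Contacting that person's colleagues as part of it tells them, in effect, who is being interviewed, which is what Section 2.3.1 says will not happen.

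This matters because Section 7.1.1 names breach of confidentiality as the only possible adverse event of the study, and Section 7.2 makes a breach reportable to the IRB within 5 working days. A protocol should not contain an instruction that could produce that event if carried out as written.

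The data-sharing text raises a related problem. A participant cannot be told accurately both that only the research team will have access to the data and that outside users may obtain a de-identified copy.

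**Working it through.** No sample size, power or margin is involved, so the check is a comparison of texts plus simple counts.

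**Step 1. Does Section 10.1 conflict with the confidentiality promises?**
- Who is told: the interviewee and that person's office staff.
- When: during informed consent, which Section 9.4 places with the individual at the start of each interview.
- What they are told: where to report a breach. Section 10.1 does not say they are given the interviewee's name.
- Effect: because the contact is tied to one person's consent, its timing and recipients can identify that person.
- Promise affected: Section 2.3.1, which covers supervisors and clinic staff. Sections 5.3 and 9.5 cover leadership only, so they are engaged only where the office staff contacted include leadership.

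**Step 2. Whom does the sentence reach?** A client has no office staff, and the surrounding text of Section 2.3.1 is about employment and supervisors. The sentence therefore reaches provider interviewees.

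**Step 3. How many people per clinic?**
- Year 1 (Section 6.1.1): 30 staff interviews at 10 clinics; 30/10 = 3 per clinic on average.
- Trial phase (Section 6.1.1): 72 staff interviews, with at least one clinical and one executive member per clinic; 72/36 = 2 per clinic.
- These sum to 30 + 72 = 102, whereas Sections 5.5 and 10.4 give about 174 staff. The protocol does not explain the difference. The number affected is therefore 102 to 174 staff, depending on which count applies.

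**Step 4. Do the data-sharing statements agree?**
- Section 10.4, first statement: summary reports, because numbers are small and identification risk is high.
- Section 10.4, second statement: a de-identified dataset on written request under an agreement. This must be the interview dataset, since the same section rules out sharing person-level administrative data.
- Sections 2.3.1 and 2.3.2: data kept locked and accessible only to the research team.
- Section 10.2: access for research staff only.
- Section 10.1: release of analysis and results limited to aggregates that reveal nothing about an individual, a policy applied to all study data.

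The second statement in Section 10.4 does not fit the access rules in Sections 2.3.1, 2.3.2 and 10.2 as worded, and sits badly with the aggregate rule. This dataset covers clients as well as staff. Client interviews number 144 in Sections 5.5 and 10.4 (144/36 = 4 per clinic) but 40 in Section 6.1.2 (40/36 ≈ 1.1 per clinic). On either count the numbers per clinic are small.

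**The case against.** **On office staff.** Section 10.1 says only that staff learn where to report a breach, not who is taking part. Clinics agree to participate before individuals consent, so a general notice to everyone at the clinic is a possible reading and would be harmless. This has force: the disclosure is an inference from the wording. But the sentence ties the notice to participating interviewees and to their consent, and Section 9.4 contains no general announcement. The harmless reading should be written down.

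**On data sharing.** Section 10.4 has real safeguards: identifiers are stripped, an approved agreement is required, and participants are to be told. It acknowledges deductive disclosure and offers the agreement as its response. The access limits in Sections 2.3.1 and 2.3.2 stand beside storage rules and could be read as covering identifiable records only. Section 2.3.2 allows individual data to be reported under a number or alias if the need arises. Section 10.4 does not itself say that summaries are the only form of sharing. All of this stands, so the inconsistency is one of scope and does not show that release is improper.

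**Stronger readings that the documents do not support.**
- A reader might infer that clients would become known to the staff who decide their take-home doses. The office-staff sentence does not reach clients.
- A reader might infer that guarded answers would bias the Aim 5 and Aim 6 findings toward favourable views of the intervention. Nothing in the protocol gives that direction; Section 2.2 reports staff concern about flexible dosing as well as support for it.
- A reader might infer that participant-level release has to be dropped. That is a trade-off for the investigators; the text requires only that one rule be chosen and stated.

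**Conclusion.** The point holds as a conflict in the text. Read plainly, Section 10.1 can reveal which staff members are interviewed, against Section 2.3.1 and outside the consent procedure in Section 9.4. It concerns provider interviewees, 102 to 174 people depending on the count used, at about 2 to 3 per clinic on the itemised figures. The conclusion assumes that the notice would be given as part of each person's consent, as written; a clinic-wide notice unconnected with recruitment would remove the problem.

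The data-sharing point is secondary. Section 10.4 has to be reconciled with Sections 2.3.1, 2.3.2, 10.1 and 10.2. Whether the consent scripts already state one rule cannot be judged, because they are not among the documents at hand.

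Neither point touches the trial's statistical analysis. H1 to H3 are tested on administrative data.

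**What to change.** 1. In Section 10.1, delete the reference to office staff so that the breach-reporting contact goes to the interviewee alone. Alternatively, replace it with a single general notice to all staff of every participating clinic, issued before recruitment, and add that step to Section 9.4.
2. Choose one sharing rule for interview data and state it consistently in Sections 2.3.1, 2.3.2, 10.1, 10.2 and 10.4. If de-identified sharing under agreement is kept, say that the research-team-only limits apply to identifiable records, and say how the summary-report statement and the aggregate rule relate to the shared file. If only summaries are intended, remove the dataset provision.
3. State the chosen rule in the consent text.

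The cost is a wording amendment with IRB review and matching consent text. Sample size and analysis do not change. Choosing summaries only would deny outside users the participant-level file; keeping the file leaves the residual deductive-disclosure risk that Section 10.4 already acknowledges.

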## Study Records Retention

All research data will be stored on secure, password-protected computers managed by NYU Langone MCIT and will be properly backed up and retained by NYU Langone Health for the period required by the NYU Langone Health’s Workforce Member IT Policy. Contact information will not be published by any means. Only trained research staff will have access to the data. Study documents will be retained for 3 years after the completion of the project in accordance with the NYU Langone policy on research data relating to projects subject to the review of the IRB.

PI will maintain all audio recordings from interviews in electronic form. Research data continuously stored in these locations will be properly backed up and retained by NYU Langone Health for the period required by the NYU Langone Health’s Workforce Member IT Policy. Contact information will not be published by any means. Only research staff will have access to the data. Study documents will be retained for 3 years after the completion of the project in accordance with the NYU Langone policy on research data relating to projects subject to the review of the IRB.

## Protocol Deviations

- Any unanticipated problems will be promptly reported to the IRB (including intentional and accidental/unintentional deviations from the IRB approved protocol) for any of the following situations:
  - *one or more participants were placed at increased risk of harm*
  - *the event has the potential to occur again*
  - *the deviation was necessary to protect a subject from immediate harm*
- ***Breach of confidentiality***
- ***Incarceration of a participant*** when the research was not previously approved under Subpart C and the investigator believes it is in the best interest of the subject to remain on the study.
- ***New Information indicating a change to the risks or potential benefits*** of the research, in terms of severity or frequency (e.g. analysis indicates lower-than-expected response rate or a more severe or frequent side effect; other research finds arm of study has no therapeutic value; FDA labeling change or withdrawal from market).

### Reporting Process

The reportable events noted above will be reported to the IRB using a Reportable New Information submission and will include a description of the event with information regarding its fulfillment of the above criteria, follow-up/resolution, and need for revision to consent form and/or other study documentation. Copies of each report and documentation of IRB notification and receipt will be kept in the Clinical Investigator’s study file.

## Publication and Data Sharing Policy

This study will comply with the NIH Public Access Policy, which ensures that the public has access to the published results of NIH funded research. It requires scientists to submit final peer-reviewed journal manuscripts that arise from NIH funds to the digital archive PubMed Central upon acceptance for publication. The principal investigator at New York University Grossman School of Medicine ([name]) will be responsible for registering the clinical trial and reporting the summary results in ClinicalTrials.gov as outlined in the NIH Policy on the Dissemination of NIH-Funded Clinical Trial Information, in order to support the NIH’s mission of broad and responsible dissemination of research. Record information will be entered within the timelines specified in the policy, i.e. initial registration of the trial no later than 21-day post-enrollment of the first participant and summary results posted no later than 12 months post-primary completion date. Additionally, informed consent documents for participants will include a statement that study will be posted on ClinicalTrials.gov. NYU Langone Sponsored Programs Administration team sets forth internal institutional guidelines to ensure compliance with NIH policy and applicable federal regulations and is available to support investigators with registering or entering summary results into the ClinicalTrials.gov database.

The data generated in this grant will be presented at national or international conferences and published in a timely fashion. All final peer-reviewed manuscripts that arise from this proposal will be submitted to the digital archive PubMed Central.

Project data will be made available to the Data Ecosystem in a manner that is consistent with Data Use Agreements with the data owners. The data owners are only permitted to share these data at the person level as long as it supports the administration of the Medicaid program. Generally, we will be able to submit reports that present statistical data at an aggregate level in a form permissible and approved by the owner. The data for the quantitative components of this study will be culled from the administrative data files of the New York State Office of Alcoholism and Substance Abuse Services (OASAS) and the New York State Department of Health (DOH). Due to the nature of the data security agreements between OASAS/DOH and NYU HEAL, we will not be able to make person-level data available for sharing. Subject to approval from the Department of Health and OASAS, we can provide tables of data summaries categorized by demographic, geographic, and provider characteristics.

We will be able to provide summary reports from qualitative data since the number of participants is small and the risk of being identification is high. The proposed qualitative research will include data from approximately 174 addiction treatment staff and 144 patients being interviewed about take-home dosing practice changes after the intervention has been implemented. The final dataset will include self-reported demographic and experience data. Even though the final dataset will be stripped of identifiers prior to release for sharing, there remains the possibility of deductive disclosure of participants with easily identifiable characteristics which could possibly affect participants’ employability. This is especially the case because the data will be collected from a small number of staff at each participating clinic and it may be known by the provider community which clinics in each identified region are participating in the study.

Thus, we will make the data and associated documentation available to users who request it in writing only under a data-sharing agreement approved by study co-investigators that provides for: (1) a commitment to using the data only for research purposes and not to identify any individual participant; (2) a commitment to securing the data using appropriate computer technology; and (3) a commitment to destroying or returning the data after analyses are completed. This data sharing plan will be made clear in consent documents for participants.

